### *6c iv. Decision to start ART*

After the baseline lab tests, physical exam, and education and counseling session, subjects will be asked to wait briefly while the study nurse reviews the laboratory and examination results and determines whether treatment can be initiated. She will then meet individually with the subject to convey the results of the lab tests and confirm that the subject still wishes to initiate ART immediately. Subjects who choose not to start ART immediately will be managed as described under "subjects requesting a delay" below.

Finally, the study nurse will write a prescription for the first month's ARVs, following South African guidelines for allowable first-line regimens. This prescription can be filled immediately at the study site's pharmacy, allowing the first dose to be taken on the same day.

### *6c v. Subjects requesting or requiring a delay*

The rapid treatment initiation process is designed to occur in one day, over a period of approximately 4-5 hours. Some patients may require more than one day, however, for example if they arrive for an HIV test late in the afternoon or cannot take several hours away from work or child care on that day but can do so later in the week. Others may need time to disclose to or obtain support from friends or family or to consider their decision. In addition, subjects with TB must have 14 days of TB treatment prior to starting ART, and some Stage 4/3 conditions may also require a short delay. These subjects will be encouraged to return to initiate ART as soon as they are able, and an appointment will be scheduled if possible. The rapid initiation process will be offered to any subject in the rapid group who returns within four weeks (28 days) of study enrollment. Subjects in the rapid group who request a delay and return more than four weeks later will be initiated under standard procedures, though they will remain in the rapid group for purposes of data analysis.

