#### *Exclusion criteria:*

- Currently on ART or on ART at any time in the past 12 months (three-drug combination; previous PMTCT regimen exposure for an earlier pregnancy is not an exclusion criterion)
- Stated intention to seek further HIV care during the next 12 months or antenatal care before completion of the current pregnancy at another site, not at the study site
- Not physically or emotionally able to participate in the study, in the opinion of the investigators
- Not willing or able to provide written informed consent to participate in the study

- Previously enrolled in the same study
- Diagnosed with drug-resistant TB or on MDR-TB treatment
- For Track 1 only, pregnant (pregnancy is an exclusion criterion for Track 1 because treatment guidelines for pregnant women differ from those for non-pregnant adults)

*\*Current South African treatment eligibility criteria for non pregnant HIV-positive adults are:*

- *CD4 count  $\leq$  350; or*
- *Tuberculosis, regardless of CD4 count; or*
- *WHO Stage 4 or Stage 3 condition, regardless of CD count (hereafter “Stage 4/3”)*

*All pregnant HIV-positive women are eligible for ART.*

Subjects in Track 1 will be followed prospectively and will be asked for written informed consent prior to study enrollment. An additional Track 1 retrospective comparison group will be enrolled comprised of patients who became eligible for ART at one of the two study sites (Thuthukani Clinic) prior to the launch of the study, with data collection limited to retrospective medical record review. In Track 2, subjects offered rapid initiation by the study clinic under the new standard of care will be followed prospectively and asked for written informed consent before study enrollment. For subjects in the comparison group in Track 2, data will be collected retrospectively through medical record review only. The study team will have no contact with these subjects, and informed consent will not be sought.

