#### *6b vi. Confirmation of treatment eligibility and study enrollment*

Under South African guidelines, ART eligibility is based primarily on CD4 count. Since a rapid CD4 count is part of the intervention for patients in the rapid group but not for those in the standard group, consent will take place before treatment eligibility is known. All subjects who meet other inclusion/exclusion criteria will be asked for consent, but only those who are treatment eligible will be enrolled in the study.

Procedures for performing a CD4 count are described below. Subjects in the rapid group will be informed as soon as their CD4 count result is available if they are eligible for treatment. Those who are not eligible on the basis of CD4 count and do not have symptoms of TB or a WHO Stage 4/3 condition will not be enrolled in the study. They will be given their CD4 count results following the clinic's standard procedures for returning laboratory results and asked to proceed with a standard pre-ART care or antenatal care visit.

Subjects in the rapid group who are eligible for treatment on the basis of CD4 count will be enrolled in the study and continue with study procedures as described below. Subjects in the rapid group who are not eligible for treatment on the basis of CD4 count but have symptoms of TB will be asked to remain in the clinic until initial TB test results are available (approximately 2 hours). Subjects who report symptoms that may indicate a Stage 4/3 condition will be examined to determine if a condition is present. Those diagnosed with TB or a Stage 4/3 condition will be enrolled in the study, while those without will be asked to proceed with a standard pre-ART care visit.

Subjects in the standard group of Track 1 will be advised to follow the standard schedule of clinic visits, which is to return to the site for their CD4 count results in 1 week. The study team will monitor CD4 count and TB test results and Stage 4/3 condition diagnoses and will enroll in the study only those who are eligible for treatment.

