#### *6c ii. TB test*

Sputum samples for patients with TB symptoms will immediately be sent to the on-site laboratory for testing using Xpert MTB/RIF. Each patient will be asked for two sputum samples to allow two Xpert tests to be run. Those with at least one positive Xpert test will be considered to have active TB. Those with two negative tests will be considered not to have TB. Those with inconclusive test results will be diagnosed clinically by the study nurse or the site doctor. Patients diagnosed with TB will be told of their results and escorted by the study assistant to the site's TB clinic, where TB treatment can be initiated.

A third sputum sample for all patients diagnosed with TB will be sent to the off-site National Health Laboratory Service laboratory for smear microscopy and culture if required. The NHLS lab results will be monitored by the study team. Any positive TB diagnosis not already made by the study nurse will be conveyed immediately to the site, and the patient will be contacted by the study assistant and asked to return to the clinic to initiate TB treatment.

The study site's standard procedures will be followed with regard to TB treatment. Under current South African guidelines, two weeks (14 days) of TB treatment is required prior to initiating ART for patients with a CD4 count  $\leq 350$  and eight weeks of TB treatment is required for patients with a CD4 count  $> 350$ . Study subjects diagnosed with TB and with CD4 counts  $\leq 350$  will be asked to return to the clinic between 14 and 28 days after study enrollment to continue with rapid ART initiation. Those returning in more than 28 days will be offered standard ART initiation. Subjects with TB and CD4 counts  $> 350$  will be advised to return for TB treatment only, then continue with standard ART initiation. Patients already on TB treatment but for less than 14 days at the time of study enrollment will also be asked to return once they have reached 14 days of TB treatment.

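### For rapid-group subjects with TB and CD4 above 350, sections 6c ii and 6c v state different TB-treatment periods before ART and different initiation pathways

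*Protocol*

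**What the plan says.** Section 6c ii (TB test) presents its rule as current South African guidance. For CD4 at or below 350, "two weeks (14 days) of TB treatment is required prior to initiating ART for patients with a CD4 count" in that range. For CD4 above 350, "eight weeks of TB treatment is required for patients with a CD4 count" in that higher range. It then gives pathways. Subjects with TB and CD4 at or below 350 come back between days 14 and 28 to resume rapid initiation. Those above 350 "will be advised to return for TB treatment only, then continue with standard ART initiation". The same paragraph closes with patients who have had less than 14 days of TB treatment at enrollment. They "will also be asked to return once they have reached 14 days of TB treatment", and no CD4 condition is attached.

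Section 6c v (Subjects requesting or requiring a delay) says that "subjects with TB must have 14 days of TB treatment prior to starting ART", again with no CD4 condition. It encourages delayed subjects to come back as soon as they can and adds: "The rapid initiation process will be offered to any subject in the rapid group who returns within four weeks (28 days) of study enrollment". Those returning later than that are initiated under standard procedures but stay in the rapid group for analysis.

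The affected subjects can be enrolled. The eligibility list in section 5c includes "Tuberculosis, regardless of CD4 count; or", and section 6b vi says, of rapid-group subjects who do not qualify on CD4 count: "Those diagnosed with TB or a Stage 4/3 condition will be enrolled in the study".

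**The concern.** For a rapid-group subject with TB and CD4 above 350, the two sections can lead to different care. Under 6c ii the subject has eight weeks of TB treatment and then standard initiation. Under 6c v as worded, the subject may be offered rapid initiation from 14 days of TB treatment if back at the clinic within 28 days of enrollment. Both the waiting period and the pathway differ.

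Three things are at stake:

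- **Treatment delivery.** What the rapid strategy gives this subgroup is not uniquely defined.
- **Consistency with the cited rule.** Section 6c ii attributes the CD4 split to national guidelines, and section 12g relies on the rapid strategy following those guidelines. The wording of 6c v does not fit both statements.
- **A secondary outcome.** How long patients with TB take to start ART is item 8 in sections 4b and 11a ii. In this subgroup it would partly reflect which section was applied.

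**Working it through.** There is no plan figure to reproduce. The check compares the two texts and adds day counts.

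**Side by side, rapid group, TB, CD4 above 350**

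| | Section 6c ii | Section 6c v |
|---|---|---|
| TB treatment before ART | eight weeks = 8 × 7 = 56 days | 14 days |
| Pathway | standard | rapid, if back within 28 days of enrollment |
| CD4 condition | yes (except the last sentence) | none |

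**Gap in the stated TB-treatment periods.** 56 − 14 = 42 days.

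**Gap in calendar time.** Let d be the days of TB treatment already completed at enrollment.

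- Remaining wait under 14 days: max(0, 14 − d). Remaining wait under eight weeks: max(0, 56 − d). The gap is the difference.
- d = 0 (TB treatment starts at enrollment): 56 − 14 = 42 days.
- d between 1 and 13: (56 − d) − (14 − d) = 42 days. This is the group in the last sentence of the 6c ii paragraph.
- d between 14 and 55: 56 − d, which falls from 42 to 1 day.
- d of 56 or more: 0 days.

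So 42 days is a maximum.

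**Position relative to the 28-day window.** With d = 0, eight weeks of TB treatment ends 56 − 28 = 28 days after the window closes. A subject offered rapid initiation inside the window would therefore start before the eight weeks in 6c ii were complete.

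**Reach into the primary outcome.** Section 11a i counts a subject as a failure if there is no six-month viral load within 10 months of enrollment. Take a month as 30.44 days, TB treatment starting at enrollment, and ART starting as soon as the stated period ends.

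- 14-day period: 14 + 6 × 30.44 ≈ 197 days, about 6.5 months. Time to spare: 304.4 − 196.6 ≈ 108 days.
- 56-day period: 56 + 6 × 30.44 ≈ 239 days, about 7.8 months. Time to spare: 304.4 − 238.6 ≈ 66 days.

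Both fall inside the 10-month window, before any further delay from standard initiation visits.

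**The case against.** The strongest defense is that 6c ii is the dedicated TB section and sets the specific rule. It moves subjects with TB and CD4 above 350 out of the rapid process before 6c v is reached. On that reading, 6c v is a shortened restatement for those who remain, and its 14 days and 28-day window match 6c ii for CD4 at or below 350. The 14 days can also be read as a minimum. A subject diagnosed at enrollment who waits 56 days satisfies it, returns after day 28, and is sent to standard procedures by both sections. There are also safeguards. In section 6c iv the study nurse reviews results and decides whether treatment can start. Section 9 requires that nurse to be qualified and authorized under national guidelines. Section 12g commits the strategy to those guidelines.

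Much of this stands. A reader might infer that the two sections can never both be followed, or that staff have nothing else to guide them. The documents support neither. The clash arises when a subject with CD4 above 350 is back within 28 days, which can happen because 6c ii tells this group to return for TB treatment.

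The defense does not remove the conflict. Section 6c v has no cross-reference and no exception, and it extends the rapid offer to everyone in the group who returns in time. Section 6e i likewise names patients with TB, without a CD4 limit, among those who may return to complete initiation. The unqualified sentence in 6c ii directly follows the CD4 split, so distance between sections does not explain it.

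**Conclusion.** The protocol is wrong as written, within a narrow scope: rapid-group subjects with TB and CD4 above 350. The stated TB-treatment periods differ by up to 42 days, and the pathway differs as well. The protocol does not say how many subjects this concerns.

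Two stronger conclusions might be drawn, and neither is supported. The first is that every such subject faces a 42-day difference. The calendar gap shrinks once a subject has had more than 14 days of TB treatment at enrollment, and it is zero from 56 days. The second is that the primary comparison is compromised. Subjects are analyzed as randomized under sections 6c v and 11b, and under the assumptions above the six-month viral load falls due inside 10 months with either period. The secondary outcome concerned is descriptive, and no sample size or error rate depends on it.

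No view is taken here on which waiting period or pathway is right.

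**What to change.** Reconcile sections 6c ii and 6c v so that one rule, stated by CD4 group, applies throughout. It should explicitly cover patients already on TB treatment at enrollment. State which subjects the 28-day rapid window covers, and align the mention of patients with TB in section 6e i. The sponsor's clinicians should decide the content of the rule.

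The cost is protocol wording only. Sample size, randomization and the primary analysis are unchanged.

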### 6d. Standard ART initiation procedures (Track 1 standard initiation group)

Subjects in the standard initiation group of Track 1 will receive standard care as provided by the study site. The right side of Figure 2 illustrates these procedures.

#### *6d i. Determination of treatment eligibility*

Following the study site's usual procedures, subjects in the standard group will be asked to give a blood sample for a CD4 count on the day they test positive for HIV. Samples are sent to an off-site laboratory for processing, with results typically available in approximately one week. Patients are then asked to schedule a return visit one week later to receive their CD4 count results and be informed of their eligibility for ART.

For study subjects receiving standard care, with whom the study team will have no direct contact after study enrollment, laboratory results will be monitored to determine those who are treatment-eligible and should be enrolled in the study. No further data will be collected for subjects who are not eligible for treatment. Follow up of those who are eligible for treatment will be by passive record review only, as described below.

#### *6d ii. Remaining ART readiness and initiation steps*

Subjects who are eligible for treatment will follow the site's standard procedures for initiating ART, based on South African guidelines. These include 1-3 return visits to the clinic for remaining laboratory tests (creatinine, full blood count, ALT, pregnancy, syphilis), TB diagnosis and treatment if required, adherence counseling, wellness education, and a physical exam. Medications will then be prescribed by the site doctor or primary health care nurse and dispensed by the site's pharmacy.

### 6e. Follow up

#### *6e i. Direct study interaction*

Direct study interaction with Track 1 study subjects will cease as follows:

- *Rapid group (Track 1)*: upon completion of the ART initiation steps described above. For most subjects, this will be at the end of their initial visit, though some may return a second time to complete the initiation procedures (e.g. patients with TB or those requesting a delay).
- *Standard group (Track 1)*: after randomization, at which point subjects will be managed by the study site following standard procedures.

From these points on, all subjects, regardless of which type of initiation they received, will be managed by the site following its routine procedures for pre-ART and ART care. Because this study evaluates routine practice and uses retention in care as an outcome, any further study interaction with subjects would affect the results, in particular loss to follow-up. There will therefore be no post-baseline study visits, only routine care visits not involving study personnel. Standard procedures will also be implemented by the study site (not the study team) for study subjects who miss scheduled visits.

Under current guidelines, adult ART patients return for routine clinical consultation visits in months 1, 2, 3, and 6 (and six-monthly thereafter). During these visits, patients have a medical exam and receive a supply of medications. All medications will be provided by the treatment site under usual treatment guidelines. A routine viral load measurement is conducted at the 6-month visit. Patients must typically return to the clinic every 1-3 months for medication pickups, whether or not they are due for a clinical consultation.

#### *6e ii. Medical record follow up*

Study subjects will be followed through review of routine medical records kept by the study site for a minimum of 10 months after the date of enrollment in the study for Track 1. This will allow all subjects who initiate ART within 3 months of study enrollment to reach the point at which the routine 6-month viral load is called for, with an additional month allowed for the viral load test to be completed. Subjects will continue to be followed until the final date of study data censoring, up to a maximum of 24 months after study enrollment.

In the study team's experience at other clinics in South Africa, a few patients who remain in care and make a clinic visit at the point at which the routine 6-month viral load test should be done do not have viral load results reported in their medical records. Should this happen, the subject's paper file and laboratory records at the site will be reviewed to confirm that no viral load test was done. If no test was done, a note will be placed in the subject's clinic file to remind clinic staff to ask the subject to provide a sample for viral load testing when she or he next comes to the clinic for routine medication pickup, which typically takes place every 2-3 months.

A blank consent form addendum will be placed in each Track 1 subject's clinic file to be used if the subject's care is being transferred to another clinic. The addendum will request consent to collect medical record data during the follow up period from the new clinic. It will be administered by study staff only if a transfer is being processed.

#### 6f. Retrospective comparison group

As a second comparison group for Track 1, in addition to the standard group, data will be collected retrospectively for a sample of patients who were determined to be eligible for ART at Thuthukani Clinic during the 12 month period preceding the start of Track 1 enrollment. As there were no major changes to South African treatment guidelines during this period, the retrospective comparison group will provide information about uptake of ART before any study-related changes were made at the clinic.

Eligible subjects for the comparison group will be selected from the HIV counseling and testing (HCT) register maintained by the study clinic. This register indicates patients newly found to be ART-eligible from among those receiving an HIV test or a pre-ART CD4 count. Patients who became eligible over the period April 2012-March 2013 will be enrolled consecutively, starting with the later date and working backward in time until the target sample size is reached. Follow up data on pre-ART care, ART initiation, retention on ART, and viral suppression at 6 months will then be collected from the site's ART clinic files and electronic medical record system. Each subject will be followed for a 10-month period from the date at which the clinic determined that the patient was eligible for ART, corresponding to the 10-month primary outcome indicator for Track 1. A temporary identifier linking the HCT register record to the follow-up records will be created and retained until all data pertaining to an the individual study subject have been collected and quality checked. Because all data will already exist at the time the sample is selected, the identifier will serve only to link records at the same site, and all records can be accessed on site, at the same time, the identifier for any individual subject will be kept for a very short period.

Procedures for collecting data for this group will be similar to those used for the Track 2 retrospective group, described below. The study will have no direct interaction with subjects in this group.

## 7. Procedures for Track 2

Track 2 of the study is a pre/post observational evaluation of immediate treatment initiation for pregnant women. New national guidelines introduced in South Africa in April 2013 call for ART to be initiated immediately, at the first antenatal clinic visit, for all pregnant women regardless of CD4 count. This guideline change provides an opportunity to evaluate the impact of rapid ART initiation for this population using an observational approach, by comparing treatment outcomes before and after the change was implemented. The much simpler study design required for a pre/post observational study is described below.

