#### 5b. Study site

The study will be conducted at:

1. Thuthukani Primary Health Clinic, Ivory Park, South Africa. Thuthukani is public-sector primary care clinic and HIV comprehensive care management and treatment (CCMT) site under the authority of the

City of Johannesburg and the Gauteng Province Department of Health. It is located in a densely-populated, under-served community in the area between Johannesburg and Pretoria known as Midrand. Thuthukani maintains a large antenatal care clinic with prevention of mother-to-child transmission (PMTCT) services and provides TB treatment and other primary care.

By July 2012, Thuthukani had started almost 7000 adult patients on ART. It currently initiates roughly 840 non-pregnant adult patients and 120 pregnant women onto ART annually. Thuthukani was selected as an appropriate site for this study due to the availability of general outpatient HIV testing, HIV testing for pregnant women, TB treatment, and ART in a single facility, allowing rapid initiation for both study populations at a single site. It is a primary health clinic located in a densely-populated, under-served, township setting typical of urban sub-Saharan Africa, and study results should thus be generalizable to other areas of South Africa and the region.

2. Themba Lethu Clinic, Helen Joseph Hospital, Johannesburg. Themba Lethu Clinic (TLC) is a public sector HIV comprehensive care management and treatment (CCMT) site located in an academic hospital under the authority of the Gauteng Province Department of Health. It serves an urban population in Johannesburg and is one of the largest HIV clinics in the country, initiating nearly 10,000 adult patients onto ART annually. It was selected as a site for Track 1 of this study due to its large patient volume, existing point-of-care laboratory infrastructure, and difference in facility characteristics from the other study site (Thuthukani). It is typical of a large hospital-based HIV clinic in South Africa.

Thuthukani Primary Health Clinic and Themba Lethu Clinic both fall under the FWA of the University of the Witwatersrand Human Ethics Review Committee (Medical). A letter confirming the local government authority's agreement for each site to participate in this study will be submitted to the BUMC IRB and Wits HREC prior to study enrollment at that site.

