## 10. Sample Size

Track 1: In a recent study we conducted in Johannesburg, we found that among patients eligible for ART, 46% initiated ART within 16 weeks of eligibility. In an analysis of data from the same Johannesburg site, we estimated that among more than 3000 patients initiated on ART in 2010 and 2011 who remained in care, 77% were virally suppressed at the routine 6-month viral load. We would thus expect approximately  $0.46 \times 0.77 = 35\%$  of those eligible to have both started treatment and be virally suppressed by the 6-month viral load. For our study site we conservatively estimate that 50% of those eligible for treatment in the standard group will be suppressed by 10 months after their HIV test. We anticipate that the rapid initiation strategy will increase the proportion suppressed to 70%.

For our primary analysis, using an  $\alpha$  of 0.05, power of 90%, 1:1 randomization, and an uncorrected Fisher's exact test, we would need to enroll 124 HIV positive ART-eligible subjects per group (248 total). We expect 70% of all HIV-positive patients to be eligible for ART under current South African guidelines on the day they test positive for HIV or make their first HIV care visit, based on results from published studies in South Africa. Therefore to reach 124 subjects per arm who are treatment eligible on the day of testing we will need to consent 177 subjects per group (354 total). To allow stratification in the analysis by sex and by site, we will consent up to 300 per group (600 total) to have adequate power. We will enroll in the study up to 67% of this total (enrollment=400).

The sample size for the Track 1 retrospective comparison group will be 120. This group will be limited to patients already found to be eligible for ART at one of the two study sites (Thuthukani). They will be compared with each of the two randomized prospective groups (rapid and standard). We expect that Thuthukani will account for approximately 60% of total prospective enrollment of 400, or 120 in each of the randomized prospective groups. We will thus aim to enroll the same the number of subjects into the retrospective comparison group as in each prospective group.

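### The Track 1 retrospective group is filled backward from March 2013, so most of its 10-month follow-up would be observed during the trial it is meant to precede

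*Protocol*

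**What the plan says.** Protocol section 6f adds a retrospective comparison group to Track 1, made up of patients found eligible for ART at Thuthukani "during the 12 month period preceding the start of Track 1 enrollment". The calendar window for eligibility runs from April 2012 to March 2013. As to the order of filling, subjects "will be enrolled consecutively, starting with the later date and working backward in time until the target sample size is reached". Each subject is followed for 10 months from the date the clinic determined eligibility. The data collected are pre-ART care, ART initiation, retention and 6-month viral suppression.

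The same section gives the purpose: the group is to supply "information about uptake of ART before any study-related changes were made at the clinic". It also says that guidelines did not change in any major way during the window.

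Section 10 sets the size ("The sample size for the Track 1 retrospective comparison group will be 120") and says the group will be compared with each randomized arm. Section 5b describes the clinic's volume: "It currently initiates roughly 840 non-pregnant adult patients and 120 pregnant women onto ART annually".

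**The concern.** Uptake, retention and suppression all happen after eligibility. A group meant to show them before the study needs its follow-up, and not only its entry date, to lie before the study. Section 6f fixes only the entry date. It then fills from the end of the window closest to Track 1, where the overlap is greatest.

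If most outcomes accrue while Track 1 is running in the same clinic, the group is close to a concurrent one. Site staff would by then be telling potentially eligible patients about immediate initiation (section 6b i), and fliers would hang in the testing and reception areas (section 12d). If the group resembled the standard arm, that could not show that standard care was unchanged by the study's presence.

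There is also a membership problem. Section 6b i recruits patients who give blood for a CD4 count or return for a result of 350 or below. A patient entered in the register in early 2013 who has not started ART could do either once Track 1 is open, and be randomized, possibly to the rapid arm. Section 6f does not say how such a patient is handled. Counting the patient in both groups, or removing only those who came back, would each distort the comparison.

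**Working it through.** **Inputs**
- Group size 120 (section 10). Check: 60% of 400, split over two arms = 0.60 × 400 / 2 = 120, which matches.
- Track 1 start: the window is the 12 months before enrollment and ends in March 2013, so the start is taken as 1 April 2013.
- Follow-up: 10 months from eligibility (section 6f).
- Clinic volume: 840 non-pregnant ART starts a year (section 5b), or 840 / 12 = 70 a month. This is a proxy, because sampling is from the HIV counseling and testing register and its monthly yield is not given.
- Share of eligible patients who start: 46% within 16 weeks, from an earlier Johannesburg study (section 10). The eligible flow would then be 70 / 0.46 = 152 a month.
- Delay from eligibility to ART: 42 days on average among those who start within 16 weeks, at the study team's Johannesburg site (section 3b); 42 / 30.4 = 1.38 months.

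**Formulas.** Let W = 120 / (eligible patients per month) be the time needed to fill the group, with eligibility dates spread evenly over the last W months before 1 April 2013.
- Mean share of follow-up after that date = 1 − W/20, for W up to 10 months. For W = 12 it is (10 × 0.5) / 12, because subjects in the earliest two months contribute nothing.
- Share of ART starts before that date, with a constant 42-day delay = (W − 1.38) / W, or zero if negative.
- Share of 6-month viral loads before that date = (W − 1.38 − 6) / W, or zero if negative.

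**Results**

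| Eligible per month | W (months) | Follow-up after 1 April 2013 | ART starts before | 6-month viral loads before |
|---|---|---|---|---|
| 152 (46% start) | 0.79 | 96% | 0% | 0% |
| 70 (all start) | 1.71 | 91% | 19% | 0% |
| 35 | 3.43 | 83% | 60% | 0% |
| 20 | 6.00 | 70% | 77% | 0% |
| 10 (whole window needed) | 12.00 | 42% | 88% | 38% |

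At 70 a month, even the earliest subject has 1 − 1.71/10 = 83% of follow-up after 1 April. The mean share is at least 90% when W is 2 months or less (120 / 2 = 60 a month or more). It exceeds 50% when W is under 10 months (more than 12 a month). At 20 a month or more, no 6-month viral load can precede April even with no delay to ART, because W does not exceed 6 months.

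**What no overlap requires.** For a 10-month window to close before 1 April 2013, eligibility must be dated no later than about the end of May 2012. That leaves the first two of the 12 months, at the opposite end from where filling begins. Two months yield 120 at 60 or more a month. Sampling forward at 70 a month, the group is complete about 22 May 2012 and its last follow-up closes about 22 March 2013.

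**The case against.** Filling backward is a recognised choice for a historical comparator, because it keeps the calendar gap to the randomized arms small. The group is also peripheral: it appears in none of the objectives in section 4 or the outcomes in section 11a. Its members are picked after their data exist and have no contact with the study, and rapid procedures are delivered individually by study staff to the rapid arm. Any influence of the trial on them would be indirect, and the protocol gives nothing from which to size it. The 91-96% also rests on a proxy: register capture and the exclusion criteria could bring the yield below 70 a month.

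All of this stands as a limit on severity and precision. It does not reconcile the purpose sentence with the fill rule. At the lower yields most ART starts would precede April, but at 20 a month follow-up time is still 70% inside the trial period and no 6-month viral load precedes it.

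Three stronger readings are tempting and are not supported.
- **Guideline change.** A reader might infer that the group is also spoiled by the April 2013 revision. Section 7 says "New national guidelines introduced in South Africa in April 2013 call for ART to be initiated immediately", but sections 5a and 7 describe this only for pregnant women, whom Track 1 excludes. No effect on care of non-pregnant adults is shown.
- **Lost-patient referral.** A reader might infer that study-assisted tracing raised this group's retention. Section 12a i confines that help to study subjects, and these patients were not study subjects during their 10 months.
- **Follow-up clock.** A reader might want the 10 months counted from the HIV test or CD4 draw. Sections 6e ii, 11a i and 11c largely count from enrollment, which sections 6b vi and 6c iii tie to confirmed eligibility. The eligibility date in 6f is a reasonable parallel.

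**Conclusion.** The point holds for this comparator. Section 6f says the group describes uptake before study-related changes, but its sampling rule places most of the observation after Track 1 opens at the same clinic. With clinic volume as the proxy, 91-96% of follow-up, at least 81% of ART starts (100% − 19%) and all 6-month viral loads fall after 1 April 2013. Across yields of 35, 20 and 10 a month, the follow-up share is 83%, 70% and 42%.

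The assumptions are a Track 1 start at the beginning of April 2013, evenly spread eligibility dates and, for ART starts and viral loads, a constant 42-day delay taken from another site. Whatever the yield, any subject eligible after about May 2012 has some follow-up inside the trial period.

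The randomized primary comparison and its sample size are untouched. This is a defect in a secondary, non-randomized comparison, easily corrected, and not a threat to the trial's main result.

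**What to change.** In section 6f, require that each subject's 10-month follow-up ends before Track 1 enrollment starts, which on the protocol's dates means eligibility no later than about the end of May 2012. One way is to enroll consecutively forward from 1 April 2012 until 120 is reached. At 60 or more eligible patients a month this gives 120 with no overlap, and the question of later randomization does not arise within the follow-up window.

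Check the register's monthly yield first. If it is lower and the group must run past May 2012, report the share of follow-up that overlaps Track 1. State in advance that any subject later randomized in Track 1 is excluded, or censored at randomization, and report how many there were, since removing them selects on return to care.

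The change takes a sentence or two and uses the same register, records and sample size. The price is a comparator up to about a year older than under backward filling, so more calendar drift is possible. Section 6f's own statement that guidelines were stable over the window lessens that worry for the period in which the group would be observed.
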